#### Day 7 repeat patient measures

On Day 7, the patient will complete repeat measures of the QUAL-EC questionnaire and the NCCN Distress Thermometer. The researcher will interview the patient using the family meeting patient semi-structured interview schedule if a family meeting has been held. If the patient participates in a family meeting after Day 7, the researcher will undertake the interview at a convenient time for the patient.

#### Day 14 repeat family measures

On Day 14 participating family member(s) follows the same intervention site procedures concerning repeat measures. If the family member(s) has attended a family meeting, the family member will complete the Family Meeting Family Feedback Questionnaire on-site or by telephone. A sample of family members (*n* = 10) will participate in an interview, using the QUAL-E (Family) questions as per the intervention site procedures.

The researcher will consult regularly with clinicians to promote participant retention and ensure complete follow-up. Incomplete participant data and the reasons for this will be documented. Pre- and post-measures that are not completed when a participant withdraws from the study will be excluded from the data analysis.

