**Methods:**

The study is a mixed-methods quasi-experimental design with pre-planned Patient-Centred Family Meetings at the intervention site. The patient will set the meeting agenda a priori allowing an opportunity for their issues to be prioritised and addressed. At the control site, usual care will be maintained which may include a family meeting. Each site will recruit 20 dyads comprising a terminally ill inpatient and their nominated family member. Pre- and post-test administration of the Distress Thermometer, QUAL-EC, QUAL-E, and Patient Health Questionnaire-4 will assess patient and family distress and satisfaction with quality of life. Patient, family, and clinician interviews post-meeting will provide insights into the meeting feasibility and outcome measures. Recruitment percentages and outcome measure completion will also inform feasibility.

Descriptive statistics will summarise pre- and post-meeting data generated by the outcome measures. SPSS will analyse the quantitative data. Grounded theory will guide the qualitative data analysis.

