### Control

The Patient-Centred Family Meeting will not be offered at the control site. Usual care will be maintained which may include a family meeting that is held as part of the facility’s usual care. The need for a family meeting will be determined as per the facility’s usual clinical practice. A proportion of these “standard” family meetings will be observed using the family meeting observation sheet.

For both the intervention and control sites, if, following consent, the patient’s mental state changes, the researcher or clinical trials nurse will consult the clinical team concerning the appropriateness of the patient continuing in the study. The clinical team will be asked to consider the patient’s mental state to assess if the patient fulfils the exclusion criteria of cognitive impairment. If the patient does fulfil the exclusion criteria, the patient will be withdrawn from the study. The family member(s) participating in the study will be informed and the family member will also be withdrawn from the study.

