#### Qualitative data

All qualitative data will be reviewed prior to the commencement of analysis. Patient interviews will be recorded and transcribed verbatim. Data analysis will be conducted using theoretical and procedural direction from grounded theory research utilising the constant comparative method [34]. The transcripts will be uploaded into the software program QSR NVivo. Open, axial, and selective coding will be used to analyse the data [35]. Iterative data analysis will commence after the first interview with all investigators participating using the selected interview transcripts and additional excerpts to identify and agree upon emergent themes. The open-ended responses from the family feedback questionnaires will be analysed using the constant-comparative method. The clinician focus groups will be recorded, transcribed verbatim, and analysed using the constant comparative method. Sufficient numbers of clinicians will participate in focus groups to ensure that data saturation is achieved.

Additional analysis of the percentage of dyads recruited, family meeting observations and feedback from patients, families and clinicians will provide information about the feasibility of the meetings. The percentage of completed questionnaires, patient and family feedback, preferences and issues about the measures will provide information about their feasibility and suitability from the patient and family perspective.

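### The withdrawal exclusion may inflate questionnaire completion because its reach is unstated, and linked family withdrawal loses obtainable Day 14 family data

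*Protocol article*

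**What the plan says.** Four places in the protocol article bear on this.

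- **Day 14 repeat family measures (control arm), closing paragraph.** "Incomplete participant data and the reasons for this will be documented". The next sentence is the rule at issue: "Pre- and post-measures that are not completed when a participant withdraws from the study will be excluded from the data analysis".
- **Statistical methods, Qualitative data.** "The percentage of completed questionnaires, patient and family feedback, preferences and issues about the measures will provide information about their feasibility and suitability". No denominator is given. The abstract agrees: "Recruitment percentages and outcome measure completion will also inform feasibility".
- **Control, second paragraph, which covers both sites.** It deals with a change in the patient's mental state after consent, judged against the cognitive-impairment exclusion. "If the patient does fulfil the exclusion criteria, the patient will be withdrawn from the study". Then: "The family member(s) participating in the study will be informed and the family member will also be withdrawn from the study". No other trigger for withdrawing the family member is stated.
- **Day 14 repeat family measures (intervention arm).** The family feedback questionnaire, QUAL-E (Family), Distress Thermometer and PHQ-4 are collected on Day 14, by telephone if needed. The control arm follows the same procedure for the repeat measures, and its feedback questionnaire, due only if a family meeting was attended, can also be taken by telephone.

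**The concern.** Assessing whether the measures are suitable and feasible is primary objective (iii) under Objectives, although Outcomes calls it the secondary outcome. A planner of the phase III trial will want to know what share of patients and families who consent can complete each measure, and why the rest do not. A form left blank because the participant withdrew is part of that answer. A rule that takes such forms out of the data analysis, placed beside a completion percentage with no denominator, leaves open whether they are counted.

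The second rule raises a different problem. The Distress Thermometer and PHQ-4 record the family member's own distress, and the feedback questionnaire records that person's experience of the meeting. None of these needs the patient to be cognitively intact on Day 14. Withdrawing the family member loses them, and does so only where the patient has declined. Acceptability, benefit and burden, which are primary objectives (i) and (ii), would then be judged with those families under-represented.

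**Working it through.** **Stated figure.** Sample size gives 20 dyads per site: 20 × 2 = 40 participants per site, and 40 × 2 = 80 in total. This reproduces. The article states no completion, withdrawal or power figure, so there is nothing else to reproduce.

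**Completion percentage.** Let n be the number consented, W the number withdrawn before the measure is due, and c the share of those remaining who complete it.

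- Withdrawn removed from the denominator: c(n − W)/(n − W) = c
- All consented in the denominator: c(n − W)/n = c(1 − W/n)
- Difference: c × W/n

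The article gives no W, so the range of 10% to 50% is an assumption. For 20 patients at one site with c = 1:

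| Withdrawn | Withdrawn removed | All consented | Difference (points) |
|---|---|---|---|
| 2 | 18/18 = 100% | 18/20 = 90% | 10 |
| 4 | 16/16 = 100% | 16/20 = 80% | 20 |
| 6 | 14/14 = 100% | 14/20 = 70% | 30 |
| 8 | 12/12 = 100% | 12/20 = 60% | 40 |
| 10 | 10/10 = 100% | 10/20 = 50% | 50 |

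With c near 90% the pattern is the same:

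- 2 withdrawn: 16/18 = 88.9% against 16/20 = 80.0%, a gap of 8.9 points.
- 6 withdrawn: 13/14 = 92.9% against 13/20 = 65.0%, a gap of 27.9 points.
- 10 withdrawn: 9/10 = 90.0% against 9/20 = 45.0%, a gap of 45.0 points.

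If the percentage is already taken over all consented, the difference is 0 in every row.

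**Linked family withdrawal.** If k patients at a site are withdrawn for cognitive impairment before Day 14, at most 20 − k nominated family members can complete the Day 14 measures. For k = 1, 2, 4 and 6 (assumed) the ceiling is 19, 18, 16 and 14 of 20, or 95%, 90%, 80% and 70%. The rule sets this ceiling whether or not the family members could have answered.

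**Timing.** At the intervention site the meeting falls on days 5–10 and the patient repeats the measures 24–48 h later, so between about day 6 (5 + 1) and day 12 (10 + 2). That leaves 14 − 12 = 2 to 14 − 6 = 8 days before the family measures are due. At the control site patient repeat measures are on Day 7, leaving 14 − 7 = 7 days. A patient can therefore attend the meeting, complete everything asked, become impaired afterwards, and the family member is still withdrawn.

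**How the two rules meet.** A family member withdrawn in this way leaves Day 14 forms uncompleted on withdrawal, so those forms fall under the exclusion too. On the wider reading of the exclusion, they disappear from the completion result as well as from the score data.

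**The case against.** The strongest reply is that the exclusion is only a missing-data rule for scores. A form nobody filled in cannot enter the means, medians and group comparisons under Quantitative data, and the completion percentage is listed separately as an additional analysis. The sentence just before the exclusion undertakes to document incomplete data with reasons, so a percentage over all consented participants remains possible. A journal article may also leave a denominator to the full protocol. This reply largely stands, and it is why the overstatement is conditional. A missing denominator alone would be no finding. The difficulty is that the article does state an exclusion from the data analysis and does not confine it to scores.

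On the family rule, the reply is that the study is built on dyads, the withdrawal is deliberate, and QUAL-E (Family) asks the relative to report on the patient, so continuing after the patient leaves raises a consent question. That is fair for the items about the patient. It carries little weight for the Distress Thermometer, the PHQ-4 and the meeting feedback, which concern the family member.

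A reader might infer more than the text supports:

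- That completed pre-tests are discarded on withdrawal. The rule names only measures not completed.
- That the family member leaves whenever the patient does. Only cognitive impairment is stated.
- That withdrawal is the main cause of non-completion, or that the results describe only dyads who stayed well. No withdrawal rate is given, and eligibility limits early decline: expected survival of at least 14 days, a performance score of at least 30 and a non-terminal phase.
- That completion is the headline result. It is one of several feasibility sources, and Outcomes assigns the primary outcome to qualitative data.

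**Conclusion.** The concern holds in two parts of unequal certainty.

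The completion percentage can be overstated, but the article does not establish that it will be. On the wider reading of the exclusion the inflation is c × W/n: 10 to 50 points for 2 to 10 withdrawals among 20 if all who stay complete, and about 9 to 45 points if roughly 90% of them do. On the narrower reading it is zero. The withdrawal counts are assumptions, so the true size is unknown.

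The loss of Day 14 family data does not depend on how the exclusion is read. Followed as written, the Control section gives up one nominated family member for each patient withdrawn for cognitive impairment before Day 14, and any additional participating relatives as well. The loss is selective, because it falls on families of patients who have declined. How many dyads this affects cannot be told from the article.

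Both parts should be fixed before the results are used to plan the phase III trial. Neither invalidates a feasibility study with no power calculation.

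**What to change.** 1. In the closing paragraph of the control arm's Day 14 section, limit the exclusion to analyses of scores.
2. Under Statistical methods, state that completion of each outcome measure is reported at each time point over all consented participants at that site, with withdrawal, death and discharge counted as not completed and shown by reason. The reasons are already to be documented, so no new data are needed.
3. In the Control section, amend the linked withdrawal so that a family member who consents may still be offered the Day 14 self-report measures and the feedback questionnaire, where one is due, after the patient is withdrawn. Whether the QUAL-E (Family) items about the patient continue should be settled with the consent wording.

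The second change needs the third beside it. Otherwise the family completion rate would count as failures people whom the plan itself stopped following.

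The cost is a completion rate that looks less favourable, a line in the family consent form and a few extra telephone contacts.

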### Data management

All patient and family participants in the VOICE Study will be allocated a unique identification (ID) code that will be entered on all questionnaires and linked with all completed interviews. The relevant ID code will form part of the data entry for the qualitative and quantitative data. All data will be entered and stored on a secure computer hard drive that will be backed up daily and be firewall protected. All computers will be password protected. Only the researcher and her supervisor(s) will have access to the master list that links participants to the de-identified data and all data will be stored separately from the register of participants. All VOICE Study documentation will be placed in a locked filing cabinet in a locked office, in accordance with National Health and Medical Research Council (NH&MRC), Australia requirements [33].

### Statistical methods

Quantitative measures and qualitative data collected for the four study groups will be analysed.

#### Quantitative data

Prior to analysis of the quantitative date, all variables will be assessed for accuracy of input, plausibility of means and standard deviations and out-of-range and missing values. The quantitative data will be analysed using Statistical Package for the Social Sciences (SPSS). Descriptive statistics (frequencies, means and medians) will be used to summarise the baseline and follow-up data including demographics, NCCN DT, PHQ-4, QUAL-EC and QUAL-E (Family) measures and quantitative questions on the feedback questionnaires. Differences on these variables [NCCN DT, PHQ-4, QUAL-EC and QUAL-E (Family)] between the intervention group and control group will be assessed using univariate, parametric or non-parametric statistics depending if these outcomes are normally or non-normally distributed.

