### Research design

The VOICE Study Research Protocol (Version 5.6, 11.3.2017) will utilise a mixed methods quasi-experimental (pre-post-test) design. The specific strategy used to mitigate factors that may compromise internal validity will be a non-equivalent control group design. This design incorporates a comparison (control) group and collection of equivalent pre-test and post-test measures for the intervention and comparison (control) groups [28]. The SPIRIT checklist [29] was used to inform the study protocol and is included as an additional file.

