## Methods/Design

### Study setting

Two sub-acute facilities in Sydney, Australia who provide specialist inpatient and community palliative care to the local geographic population will be included in the VOICE Study with one being a control site and the other the intervention site. The study design will incorporate four study groups:(i)Inpatients receiving the intervention of a planned Patient-Centred Family Meeting;(ii)Family member(s) (or equivalent person) who are invited by the patient to participate in a Patient-Centred Family Meeting;(iii)Inpatients receiving standard care (who may also participate in a “standard” family meeting);(iv)Family member(s) (or equivalent person) nominated by the patient to participate in the VOICE Study.

The control site will provide their usual palliative care, which may or may not include a family meeting. This control site will provide insights into standard palliative care practices, such as how the team determines who needs a family meeting. The intervention site will provide a planned Patient-Centred Family Meeting for patients and families. The same outcome measures will be collected at each site to help identify factors or confounding variables that operate in standard palliative care practice that may not be apparent at the intervention site. For the purposes of this research study, “family” is defined as whomever the patient designates as “family” and may include close friends or carers or significant others [10].

At each facility, the Director of the Palliative Care Service will act as the on-site Principal Investigator and will liaise with the on-site palliative care clinical staff and the PhD student (corresponding author). The other authors will be supervising the PhD student for the VOICE Study and will be involved in decisions concerning data management and publications and consultation with the on-site principal investigators as required.

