### Sample size

Twenty inpatients will be recruited from each facility. At each site, the patient will nominate one family member (or equivalent) as the primary support person to participate in the study. A total of 20 patient-family dyads will be recruited for each site, resulting in 40 participants at each site and a total of 80 participants for the entire study. The total number may exceed this if additional family participants wish to attend the Patient-Centred Family Meeting or standard care family meeting. Data will be collected from additional family participants who consent to study inclusion. A power calculation was not undertaken as this will be a feasibility study.

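### The planned between-group tests on the four scales cannot separate the family meetings from the site, because there is one non-randomised site per arm

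*Protocol article*

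**What the plan says.** The Study setting section names two facilities, "with one being a control site and the other the intervention site". The Research design section describes the comparison as non-randomised and relies on it for validity: "The specific strategy used to mitigate factors that may compromise internal validity will be a non-equivalent control group design".

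On numbers, the Sample size section says "Twenty inpatients will be recruited from each facility", each with one nominated family member, and adds "A power calculation was not undertaken as this will be a feasibility study".

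The Quantitative data section first promises descriptive summaries of baseline and follow-up data. It then goes further: "Differences on these variables [NCCN DT, PHQ-4, QUAL-EC and QUAL-E (Family)] between the intervention group and control group will be assessed", by "univariate, parametric or non-parametric statistics depending if these outcomes are normally or non-normally distributed". Choosing the method by normality is the language of hypothesis tests, and the sentence stands apart from the descriptive one before it. It mentions neither baseline adjustment nor site. The abstract's account of the same measures is "Descriptive statistics will summarise pre- and post-meeting data generated by the outcome measures".

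**The concern.** A two-sample test of 20 against 20 treats each patient, or each family member, as an independent piece of evidence about the intervention. Here the intervention was assigned to units, one unit to each arm. Whatever else differs between the two units enters the contrast in full, and the test cannot tell it from an effect of the meetings.

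The study is meant to inform a phase III randomised trial, and the Discussion says it will bear on whether one is needed. A p-value from this comparison could mislead that decision either way: a small one taken as a signal of benefit, or a large one taken as a sign that the meetings or the scales do nothing.

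**Working it through.** **The plan's own figure.** 20 dyads × 2 people × 2 sites = 80. This agrees with the Sample size section ("resulting in 40 participants at each site and a total of 80 participants for the entire study"). The article states no significance level, effect size, standard deviation or intraclass correlation (ICC), so there is no power figure to reproduce.

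**What moves together with the arm**

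- Facility: one per arm (Study setting).
- Screening and recruiting staff: the researcher at the intervention site, clinical trials nurses at the control site (Recruitment).
- Timing of the patients' repeat measures: at the intervention site they accompany the interview 24 to 48 hours after a meeting held on days 5 to 10, so about day 6 (5 + 1) to day 12 (10 + 2). At the control site they fall on Day 7 whether or not a meeting took place. Family repeat measures are on Day 14 at both sites, so this item concerns the patient scales only.

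**Degrees of freedom for site.** Two sites in two arms leave 2 − 2 = 0 degrees of freedom for between-site variance within arm. It cannot be estimated from these data, whatever the analysis.

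**Size of the effect on the error rate (illustration).** Assumptions: two-sided 5% test, n = 20 per site, no true intervention effect, site effects drawn at random with the ICC shown. The true standard error exceeds the one used by the test by the factor

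f = √[(1 + (n − 1)·ICC) / (1 − ICC)],

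and the true error is approximately 2·[1 − Φ(1.96 / f)]. The t-test column comes from a simulation with 400,000 runs per value.

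| ICC (assumed) | f | Normal approximation | t-test, simulated |
|---|---|---|---|
| 0 | 1.00 | 5.0% | 5.0% |
| 0.01 | √(1.19/0.99) = 1.10 | 7.4% | 7.3% |
| 0.05 | √(1.95/0.95) = 1.43 | 17.1% | 16.5% |
| 0.10 | √(2.90/0.90) = 1.80 | 27.5% | 26.6% |

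The article gives no dropout rate. With 15 completers per site the simulated figures are 6.6%, 13.6% and 21.9% for the same three non-zero ICCs.

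**What this means for an interval.** An ordinary 95% interval for the difference is the same test inverted. Read as an interval for the intervention effect, it would cover about 100 − 7.3 = 92.7%, 100 − 16.5 = 83.5% or 100 − 26.6 = 73.4% of the time. Its half-width at 20 per site, 2.024 × √(2/20) = 0.64 within-site SD, contains no allowance for site.

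**Precision, a separate matter.** At 20 per site, power is about 35% for a difference of 0.5 SD, and 80% power needs about 0.89 SD: (1.96 + 0.84) × √(2/20). This bears on how a non-significant result may be read; it does not raise the false-positive rate.

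**The case against.** The other side has several good points.

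- **The authors are open about the design.** They call the groups non-equivalent, and Study setting says that collecting the same measures at both sites should help to identify confounding. The primary outcome is feasibility and acceptability, assessed with qualitative data, so these comparisons are secondary. All of this stands, but recognising confounding does not let a univariate test remove it.
- **Nothing says that a difference will be read as efficacy.** A reader might infer a planned efficacy claim, or that the observed difference will become the phase III effect size. The article states neither; misreading is a risk, not a plan.
- **A significant result need not be a site effect.** A reader might conclude that it must be. It could equally reflect the meetings, baseline imbalance or chance. The documents support only that these cannot be told apart.
- **Omitting a power calculation is acceptable in a feasibility study.** A reader might blame the missing calculation for an uncontrolled error rate. That does not follow: a small sample costs power and precision. The error problem comes from the site variance.
- **The abstract is no contradiction.** It does not say that descriptive statistics are the only analysis, and an abstract may leave out a secondary comparison.
- **The 7% to 27% rests on assumed ICCs.** It also takes the intervention effect as the target. If the question were merely whether these two named units differ, site variance would not inflate the test. That stands, and it makes attribution the core of the point, with the percentages as illustration.
- **An unseen analysis plan may settle details.** It could fix the significance level, multiplicity and baseline adjustment, so none of these is held against the article as an omission. No plan could recover site variance from two sites.
- **Quantitative data have a stated role** in judging the suitability of the measures. That role is served by completion, spread, change and correlation within each site, and it does not require a test between sites.

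**Conclusion.** The point holds in this form: the article commits to univariate between-group comparisons in a design where intervention is completely aliased with site, and partly explained alternatives (recruiting staff, patient follow-up timing) run along the same line. A between-group difference, significant or not, cannot support a conclusion about the meetings.

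The aliasing and the zero degrees of freedom follow from the design and need no assumption. The error rates do rest on assumptions: ICC between 0.01 and 0.10, two-sided 5%, 20 per site. That the sentence means hypothesis tests is the natural reading of its wording, although the article does not mention p-values. The primary, qualitative outcome is unaffected.

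**What to change.** Rewrite the last sentence of the Quantitative data section so that it:

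1. reports, for each site separately, baseline, follow-up and pre-post change for each scale: mean, SD, 95% confidence interval for the change, and pre-post correlation;
2. shows any between-site difference only as a baseline-adjusted estimate without a p-value, labelled *site and intervention combined*, with a note that its interval reflects within-site sampling error only and does not cover variation between sites;
3. states that this difference will not be used as evidence of efficacy or as the phase III effect size;
4. states that the SDs and correlations will inform phase III planning.

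The note in item 2 is essential, since dropping the p-value while leaving an unqualified interval would carry the same problem forward. The cost is the wording of one paragraph, with no new data collection; the downside is that there will be no between-group p-values to report.

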#### Quantitative measures

Measures of patient and family satisfaction with quality of life at end-of-life and patient and family distress will be collected using validated measures, and these measures will be evaluated qualitatively as described above, to assess their suitability and feasibility for patients and families.

The QUAL-EC [18] questionnaire will assess the consented patients’ symptom control, their relationship with the healthcare provider, life completion, and preparation for end-of-life. The QUAL-E (Family) [19] questionnaire will measure the experience of consented family members’ whose relatives are enrolled in the VOICE Study. The questionnaire will assess the relationship with the healthcare provider and the completion of the relationship with the patient. The family will also report on the patient’s symptom experience, preparation for death, and state of peace.

The NCCN Distress Thermometer [20] will be used to assess changes in distress of patients and family members pre- and post-patient-centred family meetings. The PHQ-4 [21–23] combines the Patient Health Questionnaire-2 and Generalised Anxiety Disorder (GAD)-2, and will be used as an additional distress measure for families.

A single question measure: “To what extent are you at peace?” will explore the patients’ spiritual and emotional well-being [30].

The use of the QUAL-EC as a patient outcome measure is based on the rationale that the quality of life at the end of life measures and domains assessed may be impacted by participation in the Patient-Centred Family Meeting. The rationale for the use of the QUAL-E (Family) tool was based on it being the companion instrument for the QUAL-EC and that it will also measure domains of the family experience that may be affected by participation in a Patient-Centred Family Meeting.

The NCCN Distress Thermometer instrument has been used previously to assess changes in distress of key family members pre- and post-family meetings [31]. The VOICE Study will provide an opportunity to assess the feasibility and suitability of the PHQ-4 tool in the context of palliative care and is not likely to be burdensome for the family member. However as it was considered an additional burden for the patient it will not be used. In the event that the scores obtained on either the NCCN Distress Thermometer or PHQ-4 indicate significant distress, the clinical team will be informed.

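### The between-group comparison is fixed as univariate, with no stated role for the pre-test on which the non-equivalent control group design relies

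*Protocol article*

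**What the plan says.** The Research design section describes a pre-test/post-test quasi-experiment and states how validity is to be protected: "The specific strategy used to mitigate factors that may compromise internal validity will be a non-equivalent control group design". It explains that this involves "collection of equivalent pre-test and post-test measures for the intervention and comparison (control) groups".

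Allocation is by facility. Under Study setting there are two units, "with one being a control site and the other the intervention site". The same section gives a reason for measuring both: "The same outcome measures will be collected at each site to help identify factors or confounding variables that operate in standard palliative care practice".

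The analysis is set out under Statistical methods, Quantitative data. Frequencies, means and medians "will be used to summarise the baseline and follow-up data including demographics". Differences between intervention and control on the NCCN Distress Thermometer, PHQ-4, QUAL-EC and QUAL-E (Family) "will be assessed using univariate, parametric or non-parametric statistics depending if these outcomes are normally or non-normally distributed". No covariate, baseline adjustment or change score is named there. The passage also does not say whether the compared quantity is the follow-up score or the change from baseline.

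Elsewhere, under Quantitative measures, the Distress Thermometer "will be used to assess changes in distress of patients and family members pre- and post-patient-centred family meetings".

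The Sample size section gives 20 dyads per site, "resulting in 40 participants at each site and a total of 80 participants for the entire study", and no power calculation.

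**The concern.** The design section and the analysis section do not connect. The first justifies the control group by the pre-test taken in both groups. The second fixes the between-group method and gives the pre-test no stated part in it beyond a descriptive summary.

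The usual meaning of a univariate parametric or non-parametric comparison of two groups is a t-test or a Mann-Whitney test. Applied to follow-up scores, either test treats the two units as exchangeable before the meeting, which the article itself says they are not. A difference already present at admission would then appear as a difference after the meeting.

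What is at stake is the quantitative signal passed to the phase III trial that the study is meant to inform. An analyst could also choose between follow-up and change scores after seeing the data, because the text permits either.

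**Working it through.** **Stated figure.** 20 dyads × 2 members = 40 per site, and 40 × 2 sites = 80. This reproduces. There is no power calculation or significance level to reproduce.

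**Inputs from the article.** 20 patients and 20 nominated family members per site, one site per arm, and the same instruments before and after at both sites.

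**Assumed inputs, not in the article.** Baseline gap between sites d = 0.5 SD (range 0 to 0.8); pre-post correlation r = 0.5 (range 0.3 to 0.7); no true effect; two-sided 5% tests; normal scores; no dropout.

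Two accounts of how a baseline gap behaves were considered:

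- *The gap regresses*: follow-up depends on the person's own baseline only, and not on site.
- *The gap persists*: the site difference is unchanged at follow-up.

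**Expected bias.**

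- Post scores: r × d = 0.5 × 0.5 = 0.25 SD if the gap regresses; d = 0.50 SD if it persists.
- Regression on site and baseline score (ANCOVA): r × d − r × d = 0 if it regresses; d − r × d = 0.50 − 0.25 = 0.25 SD if it persists.
- Change scores: r × d − d = 0.25 − 0.50 = −0.25 SD if it regresses; d − d = 0 if it persists.

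**Simulation**, 20,000 runs, 20 per group, d = 0.5, r = 0.5:

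| Analysis | Gap regresses: bias, false positives | Gap persists: bias, false positives |
|---|---|---|
| t-test on post scores | 0.25 SD, 12.2% | 0.50 SD, 34.1% |
| ANCOVA on baseline score | 0.00 SD, 5.1% | 0.25 SD, 13.6% |
| t-test on change scores | −0.25 SD, 12.0% | 0.00 SD, 5.0% |

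**False positives over gaps of 0.3 to 0.8 SD and correlations of 0.3 to 0.7:**

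| Analysis | Gap regresses | Gap persists |
|---|---|---|
| Post scores | 5.4–40.4% | 14.6–69.4% |
| ANCOVA | 4.6–5.1% | 6.4–37.5% |
| Change scores | 6.7–31.6% | 4.8–5.1% |

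With no baseline gap, all three stay at about 5%.

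In every simulated setting with a gap, ANCOVA has fewer false positives than the post-score test. Change scores do best when the gap persists but can do worse than post scores when it regresses: at d = 0.5 and r = 0.3 the rates are 14.6% against 7.5%. No method is unbiased under both accounts.

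**Precision.** The difference detectable with 80% power is (1.960 + 0.842) × √(2/20) = 0.89 SD for post scores. With baseline adjustment it is multiplied by √(1 − r²): 0.89 × √0.75 = 0.77 SD at r = 0.5, and 0.85 and 0.63 SD at r = 0.3 and 0.7. For change scores at r = 0.5 it is 2.802 × √(2 × (1 − 0.5) × 2/20) = 0.89 SD, no gain.

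**The case against.** A reader might infer that the pre-test is left out of the comparison altogether. The article does not say so. A t-test or Mann-Whitney test on change scores is also univariate and uses the pre-test, the design is labelled pre-post, and the Distress Thermometer is described as measuring change. The 0.25 and 0.50 SD biases therefore apply only if follow-up scores are compared. This part of the objection stands, and it limits the point to what the article fails to state.

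A reader might also infer that choosing the test by distribution spoils a declared error rate. The article declares no significance level and names no formal normality test, so that criticism has no target. Nor does chance imbalance between two groups of 20 count as bias, because the standard error of an unadjusted test already allows for it. Only a systematic difference between the sites matters here.

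ANCOVA is not a cure. If site differences persist, which is plausible with one distinct facility per arm, it remains biased and change scores do not. That stands, and it is why both should be reported. Adjusting for days from baseline to post-test is tempting too. But control patients repeat the measures on Day 7, while intervention patients repeat them 24–48 hours after a meeting held between Days 5 and 10. Timing is thus partly set by arm, and the covariate would be entangled with site.

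The consequence is modest: the primary outcome is feasibility and acceptability assessed qualitatively, the abstract describes the quantitative analysis as descriptive, and no decision rule depends on these comparisons. This stands and lowers the weight of the point.

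Finally, an article may leave model details to the full protocol or an analysis plan. That would answer a complaint about silence. Here the article does state a between-group method, and the method as stated does not carry out the design rationale given in the same article.

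**Conclusion.** The point holds as a mismatch between design and stated analysis. The article fixes univariate between-group statistics and gives no route by which the pre-test enters them, although the pre-test is the reason given for trusting a non-equivalent comparison. It does not show that the pre-test will be ignored.

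On the follow-up-score reading, and under the assumed 0.5 SD gap and correlation of 0.5 with 20 per group and no true effect, the bias is 0.25 to 0.50 SD and the false-positive rate 12% to 34%. Baseline adjustment lowers these rates to 5% and 14%. The size depends entirely on the assumed gap, the assumed correlation and how the gap evolves; with no gap there is no bias.

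No analysis can separate intervention from site with one site per arm. The change is worth making because it is nearly free and the results feed phase III planning. It does not affect the qualitative primary outcome.

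**What to change.** Replace the between-group sentence under Quantitative data with text to this effect:

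- Each follow-up score (Distress Thermometer, PHQ-4, QUAL-EC, QUAL-E (Family)) is compared between sites by linear regression with site and the participant's own baseline score as the only terms. The result is reported as an adjusted difference with a 95% confidence interval from robust or bootstrap standard errors. The same quantity is then estimated for every measure, with no switch of test.
- The between-site difference in change from baseline is reported beside it with its interval, because the two analyses can disagree in non-randomised groups and neither is unbiased in every scenario.
- With one site per arm, site and intervention remain confounded. The differences are exploratory input to the phase III trial and are not estimates of the intervention's effect.

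**Cost.** One residual degree of freedom per model (with 20 per site, 40 − 2 = 38 falls to 40 − 3 = 37) and a little more analysis work. The baseline scores for these instruments are already collected at both sites, so no new data are needed.
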